### Blinding

In this study, both patients with mild AD and dermatologists (investigators) will be blinded to the treatment allocation. Furthermore, the outcome assessors, data collectors, and statistician responsible for data analysis will also be unaware of the group assignment during the trial period to prevent bias.

### Intervention and Control

#### Treatment Group

Patients with mild AD in the treatment group will undergo 3 treatment sessions with HBL incorporated with CAPCS every day for 4 weeks. To ensure the correct application of HBL, we will provide individual guidance to each patient, instructing them that 1 knuckle length of HBL should be used to cover no more than 2% of the body surface area and to apply a 3-5-minute finger massage to promote its absorption. In this study, patients will also be instructed not to use any additional treatment for AD. If a patient uses additional treatment for an emergency, detailed information will be recorded and the patient will be asked to withdraw from the trial.

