#### Control Group (Placebo)

Patients with mild AD in the control group will undergo 3 treatment sessions with the placebo (HBL without CAPCS) every day for 4 weeks. The HBL placebo is produced and provided by Shell Party Innovations Technology (Shenzhen) Co, Ltd, which maintains complete consistency in HBL in terms of appearance, weight, color, odor, and package, except for the incorporation of CAPCS (Figure 1). The application, individual guidance, and instruction regarding HBL placebo use in the control group will be completely in line with that in the treatment group. Patients in the control group will also be instructed not to use any additional treatment for AD. Like before, if a patient uses additional treatment for an emergency condition, detailed information will be recorded and the patient will be asked to withdraw from the trial.

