#### Follow-Up

In this study, all patients will undergo a physical examination and skin lesion evaluation at baseline (day 0) following enrollment and then will be followed up for 4 weeks subsequently and undergo treatment efficacy evaluation at weeks 2 and 4. Detailed information about data collection, physical examination, and skin lesion evaluation is shown in Table 1.

**Table 1 table1:** Detailed information about the timeline for data collection, physical examination, and skin lesion evaluation.

Study period	Enrollment (day 1)	Baseline (week 0)	Follow-up (week 2)	Follow-up (week 4)
Informed consent	Yes	N/A^a^	N/A	N/A
Screening	Yes	N/A	N/A	N/A
Clinical assessment	Yes	N/A	Yes	Yes
Medical history	Yes	N/A	Yes	Yes
Laboratory examination	Yes	N/A	N/A	Yes
Taking photos of lesions	N/A	Yes	Yes	Yes
NRS^b^ for itching	N/A	Yes	Yes	Yes
EASI^c^	N/A	Yes	Yes	Yes
DLQI^d^	N/A	Yes	Yes	Yes
Drug use	N/A	N/A	Yes	Yes
Adverse effects	N/A	N/A	Yes	Yes

^a^N/A: not applicable.

^b^NRS: Numeric Rating Scale.

^c^EASI: Eczema Area and Severity Index.

^d^DLQI: Dermatology Life Quality Index.

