##### Adverse Events

In this study, patients with mild AD will be informed of the risks that may arise in the study before they sign the informed consent form. We have defined adverse events as unintended signs, symptoms, or diseases occurring after treatment that are not necessarily related to the intervention. The occurrence of any adverse events will be accurately recorded in the case report form (CRF). In this study, appropriate treatment will be provided by dermatologists when they encounter adverse events, and the adherence condition of patients and adverse events will be recorded.

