### Withdrawal and Dropout

According to the Declaration of Helsinki, all participants will be respected and can withdraw from the study at any time for any reason. The personal information about participants will be collected and kept confidential. In this study, patients can withdraw at any time, and the reason for withdrawal will be recorded in the CRF.

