### Ethical Considerations

This study was reviewed and approved by the Ethics Committee of Shanghai Dermatology Hospital and the Institutional Ethics Review Committee of the Shanghai Skin Diseases Hospital in 2023 (approval number 2023-33). The implementation of the study will strictly adhere to the Declaration of Helsinki. Any adverse events, violations, and amendments to the study protocol or informed consent form will be reported to the Ethics Committee of the Shanghai Skin Diseases Hospital. All patients will sign the informed consent form before enrollment, and participant information will be protected.

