### Quality Control

In this study, we will implement a series of measures to improve data quality and ensure the reliability of collected data. First, we will implement a pilot study to train all investigators participating in this study and to evaluate the reliability and validity of the CRF used for data collection. Second, we will assign two PhD students as the inspectors to conduct comprehensive checks in order to ensure the accuracy and integrity of the collected data. Third, we will actively contact all recruited patients during the 4 weeks of follow-up because frequent communication will enhance the patients’ trust and thereby increase their willingness to participate and remain in the study.

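### A patient who uses additional treatment in an emergency is asked to leave the trial, not only to stop the lotion; leaving before week 4 forfeits the only post-baseline laboratory test

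*Protocol article*

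**What the plan says.** Patients in both arms are told to use no other treatment for atopic dermatitis. For a breach in an emergency, the Treatment Group section reads: "If a patient uses additional treatment for an emergency, detailed information will be recorded and the patient will be asked to withdraw from the trial". The Control Group (Placebo) section repeats the rule for a patient who "uses additional treatment for an emergency condition, detailed information will be recorded and the patient will be asked to withdraw from the trial".

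Table 1 (Follow-Up) has four columns: enrollment, baseline, week 2 and week 4. Its two safety rows are "Laboratory examination Yes N/A N/A Yes" and "Adverse effects N/A N/A Yes Yes".

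Three other provisions bear on the point:
- Adverse Events requires any adverse event to be entered in the case report form and treated by a dermatologist.
- Withdrawal and Dropout says that "the reason for withdrawal will be recorded in the CRF".
- Quality Control says "we will actively contact all recruited patients during the 4 weeks of follow-up", and explains this as a way to keep patients willing to take part.

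The article describes no assessment at or after withdrawal.

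**The concern.** Stopping a product and leaving a trial are different acts. A patient who needed other treatment has good reason to stop the lotion, but safety observation need not end with it. The article joins the two.

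Safety is a stated objective alongside efficacy. The patients sent out by this rule are a selected group, namely those whose condition led them to other treatment within four weeks. If they leave, the week-4 laboratory results describe only the others, and the later course of the removed patients' events may be known only in part.

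**Working it through.** **Inputs.** The exit rule comes from the Treatment Group and Control Group sections, and the schedule from Table 1. The planned total of 200 and the 20% dropout allowance come from Sample Size. From Results: recruitment from January 2024 to a proposed end in July 2025, and 180 enrolled with 160 through week 2 as of May 2025.

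**Step 1: loss per patient who leaves under the rule.** Table 1 has one laboratory test after enrollment (week 4) and two adverse-effect records (weeks 2 and 4).

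| When the patient leaves | Post-baseline laboratory tests missed | Scheduled adverse-effect records missed |
|---|---|---|
| Before the week-2 visit | 1 of 1 | 2 of 2 |
| After the week-2 assessments, before week 4 | 1 of 1 | 1 of 2 |
| At week 4, if the use comes to light only then | 0 of 1 | 0 of 2 |

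The laboratory loss is complete for every exit before week 4.

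**Step 2: how many patients.** The article gives no count for this rule. The nearest figure is completion of week 2: 160/180 = 88.9%, as stated. The remainder is 180 - 160 = 20, or 20/180 = 11.1%.

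Some of these 20 were simply not yet due. Assuming even accrual over 16 to 17 months:
- monthly rate: 180/17 = 10.6 to 180/16 = 11.25
- enrolled in the last 14 days (365/12 = 30.4 days per month): 10.6 x 14/30.4 = 4.9 to 11.25 x 14/30.4 = 5.2, about 5
- due but without week 2: about 20 - 5 = 15, and 15/180 = 8.3%

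That figure covers all causes and only the time before week 2. Exits between weeks 2 and 4, which also lose the laboratory test, have no count at all. It therefore neither measures nor bounds the number leaving under this rule.

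As an illustration only, if 5%, 10% or 20% of 200 left under the rule before week 4, then 10, 20 or 40 patients would lack a post-baseline laboratory result. The 20% end equals the planned dropout allowance, which is for all causes.

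**Step 3: how many patients a change can still reach** (same accrual assumption). The last 20 patients take 20/11.25 = 1.8 to 20/10.6 = 1.9 months, which agrees with July 2025. Patients within 28 days of enrollment at any time number about 10 (twice the 14-day figure).

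| Change in force | Not yet enrolled | Still in follow-up | Reach of 200 |
|---|---|---|---|
| At the May 2025 count | 20 | about 10 | about 30 (15%) |
| One month later | about 20 - 11 = 9 | about 10 | about 19 (10%) |
| End of recruitment | 0 | about 10 | about 10 (5%) |

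**The case against.** **The full protocol may contain an exit visit.** This is possible. A reader might infer that the trial has no safety assessment on leaving; the documents do not support that, because an article condenses. The point rests on what is printed, which is a rule to leave the trial. If an exit visit with a laboratory test exists, the sponsor can say so and most of the point falls away.

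**Adverse events are recorded anyway.** This largely stands. The triggering event, the details of the other treatment and the reason for leaving are all captured. Recording of adverse events is not tied to scheduled visits, and contact covers all recruited patients for four weeks. A reader might infer that adverse events are lost outright or that the proportion with at least one event is distorted; the text supports neither. What contact cannot supply is a laboratory value or a scheduled visit record.

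**Use may come to light only at a visit.** Table 1 records drug use at weeks 2 and 4. If that row covers other treatment and not just the lotion, use found at week 2 comes with the week-2 adverse-effect record, and use found at week 4 costs nothing. That narrows the first row of the Step 1 table but leaves the second intact.

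**Laboratory values are not a named outcome, and the product is a lotion for patients with less than 5% of body surface affected.** This is correct, and it is a main reason for rating the point minor.

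**A test at stopping does not put the patient back into the week-4 results.** This is also correct: it would be taken at a different exposure time and after other treatment. The remedy should therefore prefer the week-4 visit and use a test at stopping only as a fallback.

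**Conclusion.** The point holds, as a minor one. Followed as written, the rule removes a selected group from safety observation in both arms. The firm part of the loss is the single post-baseline laboratory test and the remaining scheduled adverse-effect record or records for each patient who leaves before week 4. Loss of later adverse events is partial and uncertain.

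The number affected is unknown. A reader might take it to be negligible, but nothing in the article says so, and the Limitations section anticipates that barring other treatment could make withdrawal relatively frequent. A reader might equally take the 20 of 180 without a week-2 visit as exits under this rule. That is not supported either: the figure covers all causes and includes patients not yet due.

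The conclusion assumes that patients comply with the request to withdraw and that the full protocol adds no exit assessment. Even accrual matters only for the rough counts in Steps 2 and 3.

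**What to change.** Reword the rule in the Treatment Group and Control Group sections along these lines: a patient who uses additional treatment in an emergency stops the lotion, and the treatment is recorded. Unless consent is withdrawn, the patient stays in follow-up with the scheduled visits and adverse-effect records to week 4. The planned laboratory test is done at week 4, or at stopping if the patient will not return. Results obtained after additional treatment are flagged. The instruction not to use other treatment stays as it is, and the sample size does not change.

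The cost is a short amendment; Ethical Considerations already provides that "amendments to the study protocol or informed consent form will be reported to the Ethics Committee". No extra laboratory test is needed, since it is the one already planned, but there will be a few extra contacts. Events and laboratory values after other treatment are harder to attribute to the lotion, hence the flag. Late patients would be followed differently from earlier ones.

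Reach is the main limit: roughly 15% of patients if in force at the May 2025 count, falling to about 5% at the end of recruitment. If the full protocol already provides an exit visit with a laboratory test, stating that in the trial report would cover most of the loss; those patients would still be absent from the week-4 results.

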### Sample Size

In this study, the sample size was calculated based on the proportion of patients achieving at least 60% improvement (defined as the effective rate) in the Eczema Area and Severity Index (EASI) score from baseline to week 2 (EASI_60_) in both the treatment group and the control group. A previous pilot study (data not published) indicated that the proportion of EASI_60_ achievement at week 2 was 50% in the CAPCS group and 20% in the placebo group. In addition, a previous open-label clinical trial involving 60 pediatric patients with AD demonstrated comparable efficacy outcomes, with CAPCS combination therapy showing a 42.86% response rate versus 7.14% for the control group at week 2, with statistically significant differences (*P*<.05) [25]. In this study, we used the following formula to calculate the sample size:

We set the proportion of EASI_60_ achievement at week 2 in the treatment group to p1=45%, the proportion of EASI_60_ achievement at week 2 in the control group to p2=20%, the type I error to α=0.05, the type II error to β=0.1. The sample size calculation indicated that at least 70 patients be recruited in each group. Considering a 20% dropout rate and a 10% multicenter effect, we plan to enroll 100 patients with mild AD in each group, for a total of 200 patients with mild AD.

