### Outcomes

#### Primary Outcome

In this study, the primary outcome is set as the proportion of patients who achieve EASI_60_ at week 2. The EASI_60_ is defined at least 60% improvement in the EASI score from baseline to week 2, which is calculated as (EASI at baseline – EASI at week t)/(EASI at baseline) × 100%.

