### Statistical Analysis

In this study, all data will be recorded in the CRF and then input into a database established using Epidata 3.1 software. The full analysis set (FAS) and the per protocol set (PPS) will be analyzed using the SAS 9.2 statistical package, and missing data will be processed using the multiple imputation method. In this study, quantitative variables with a normal distribution will be expressed as means (SDs), while quantitative variables with a skewed distribution will be expressed as medians (IQRs). Qualitative variables will be expressed as frequency counts and proportions (%). We will apply the 2-sample Student *t* test or the Wilcoxon rank-sum test to examine differences between groups for quantitative variables, as appropriate, and repeated measurement data will be analyzed using repeated-measure ANOVA. The Wilcoxon rank-sum test, the chi-square test, or the Fisher exact test will be performed to examine the differences between groups for qualitative variables, as appropriate. In this study, *P*<.05 (2-tailed) will be considered statistically significant.

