### Limitations

This study may have a few limitations. First, the study period is set to 4 weeks, which limits the observation of the long-term effects of HBL incorporated with CAPCS, as well as its efficacy in prevention of disease recurrence in patients with AD. Second, differences in climate (temperature, humidity, ultraviolet radiation, seasonal changes), lifestyle habits (high-fat food consumption, high-calorie diets, tobacco smoking, alcohol drinking) and other extrinsic factors (cultural differences, occupational exposure, etc) in the 10 selected hospitals may cause information bias, which should be adjusted through sensitivity analysis and subgroup analysis. Third, patients in this study will be instructed not to use any additional treatment for AD, which might induce a relatively high rate of withdrawal in them.

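### Patients withdrawn before week 2 after emergency use of additional AD treatment fall under multiple imputation with no stated exception; under ordinary imputation this overstates each arm's EASI60 rate

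*Protocol article*

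**What the plan says.** **Additional treatment.** The Treatment Group section states what follows when other AD treatment is used in an emergency: "detailed information will be recorded and the patient will be asked to withdraw from the trial". The Control Group (Placebo) section sets the same consequence for the placebo arm.

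**Primary outcome.** Under Primary Outcome, "the primary outcome is set as the proportion of patients who achieve EASI_60_ at week 2", that is, at least 60% improvement from baseline.

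**Visits.** Table 1 schedules EASI at baseline, week 2 and week 4 only. The additional itch ratings in the NRS Score section all fall within 30 minutes of application at baseline.

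**Analysis.** The Statistical Analysis section names a full analysis set and a per-protocol set. Its rule for incomplete data reads: "missing data will be processed using the multiple imputation method". The Abstract also names multiple imputation. Neither place sets these patients apart.

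**Expected withdrawal.** The Limitations section says of the bar on additional treatment: "which might induce a relatively high rate of withdrawal in them". The only sensitivity and subgroup analyses named there concern climate, lifestyle and other extrinsic differences between hospitals.

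**The concern.** Each rule is ordinary alone, but together they make the primary outcome go missing for a reason tied to the outcome. Someone who turned to other AD treatment before week 2 is hard to call a responder to the lotion. Yet once that patient has left the trial, the week-2 EASI is likely to be absent and becomes a value to impute.

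Multiple imputation in its usual form assumes that, given the observed data, patients with missing values resemble those without. Here the observed data for an early leaver are baseline data only, so nothing in the EASI, NRS or DLQI record tells the model that the patient was doing badly. The imputed response probability is close to that of patients in the same arm who stayed.

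At stake are the two response rates to be reported for the primary endpoint and, less predictably, their difference.

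**Working it through.** **1. Inputs**
- Planning rates 45% and 20%, two-sided α 0.05, β 0.1, 70 per group enlarged to 100 (Sample Size; Statistical Analysis for two-sidedness).
- 180 enrolled and 160 with the 2-week follow-up by May 2025 (Results).
- Share *w* withdrawn before week 2 after additional treatment: not given, so a range is assumed.

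**2. The plan's own figure**

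Pooled-variance formula for two proportions: n = [1.96·√(2·0.325·0.675) + 1.2816·√(0.45·0.55 + 0.20·0.80)]² / 0.25² = 71.7, so 72 per group. The unpooled form gives 68.5, so 69. The stated 70 lies between them, and 70/(1 − 0.30) = 100. The sample size is not in dispute.

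**3. Cap on early losses**

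180 − 160 = 20, and 20/180 = 11.1%, pooled and for any reason. Some of these patients may not yet have been due at week 2. Taking about 90 per arm, losses in both arms together cannot exceed 20 patients.

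**4. Size of the overstatement**

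Let *p* be the composite rate, with these withdrawals counted as non-response. All responders are then among the stayers, whose rate is p/(1 − w). If imputation returns the stayers' rate, the arm is overstated by p·w/(1 − w).

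| Withdrawn, treatment/control | Treatment | Control | Difference (true 25.0) |
|---|---|---|---|
| 5%/5% | 0.45/0.95 = 47.4% | 0.20/0.95 = 21.1% | 26.3 |
| 10%/10% | 0.45/0.90 = 50.0% | 0.20/0.90 = 22.2% | 27.8 |
| 5%/15% | 0.45/0.95 = 47.4% | 0.20/0.85 = 23.5% | 23.8 |
| 15%/5% | 0.45/0.85 = 52.9% | 0.20/0.95 = 21.1% | 31.9 |

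Every row fits the cap: each 1% of 90 is 0.9 patients, so the last three rows use 18 patients in all and the first uses 9. The last two rows only illustrate direction; the article does not say which arm loses more.

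**5. When the sign turns**

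The difference is overstated when 0.45·w_T/(1 − w_T) exceeds 0.20·w_C/(1 − w_C). At these rates it is understated only if the control arm's withdrawal odds are more than 0.45/0.20 = 2.25 times those of the treatment arm. If the two composite rates are equal and withdrawal is equal, no spurious difference arises.

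**6. Power if these patients count as non-responders**

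Here the planning rates are read differently, as the stayers' rates, so the composite rate is p(1 − w). With 100 per arm and a pooled-variance test:
- 10%/10%: 40.5% vs 18.0%, power 94.4%.
- 20%/20%: 36.0% vs 16.0%. Power = Φ[(0.20 − 1.96·√(2·0.26·0.74/100)) / √((0.36·0.64 + 0.16·0.84)/100)] = Φ(1.30) = 90.3%.
- 20% treatment, 10% control: 36.0% vs 18.0%, power 82.3%.

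The last two use the planned 20% dropout allowance as a stress test and lie above the cap in step 3. None of the three leaves anything for the 10% multicenter allowance.

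**The case against.** **The analysis plan may settle it.** The article names multiple imputation but no model, and imputation can be done under missing-not-at-random assumptions. An analysis plan not shown could already score these patients as non-responders. This stands as a limit on certainty. The article nevertheless commits to imputation in both Abstract and Methods without exception, so the point concerns a stated rule and not absent detail.

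**The trigger is narrow.** It is use of additional treatment for an emergency, in mild disease, and only use before week 2 touches the primary outcome. A reader might infer that everyone in whom the lotion fails is withdrawn, or that frequent withdrawal is forecast. The text supports neither; the Limitations section says only that it might happen.

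**Loss of later data is inferred.** Patients are asked to leave, details are recorded, and the Quality Control section plans contact with all recruited patients over the 4 weeks. The article does not say that assessments stop, though it describes none after withdrawal.

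**Large distortions are not supported.** A reader might work through 10% vs 30% or 20% vs 5% withdrawal and find very large shifts, or a spurious difference where none exists. With about 90 per arm these need 9 + 27 = 36 and 18 + 4.5 = 22.5 withdrawals, more than the 20 patients without week-2 data. Nor do the documents show that the treatment effect is inflated: heavier loss from the vehicle arm can shrink it.

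**Bias presupposes a composite target.** The article states no estimand, so this is fair. But if the target were the response had no other treatment been used, stayers would still be a doubtful stand-in for patients who had an emergency.

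**Conclusion.** The point holds in limited form. Read as written, the plan would impute the week-2 response of patients who left after using other AD treatment, from baseline information only, at about the rate of those who stayed. Each arm's EASI60 rate is then too high. With even losses, the assumed upper case of 10% per arm overstates the rates by 5.0 and 2.2 points and the difference by 2.8 points; smaller even losses do less. Uneven losses can move the difference either way, and the documents do not indicate which.

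This rests on three assumptions: imputation is of the usual missing-at-random kind, users of additional treatment count as non-responders, and nearly all early non-completers left for this reason. The last makes 10% a high figure. Lost week-4 laboratory data are a side issue, since the stated safety outcome is adverse events.

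**What to change.** Before unblinding, state in the analysis plan:

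1. In the primary analysis of the full analysis set, a patient who used additional AD treatment, or withdrew for lack of effect or an adverse event, before week 2 is an EASI60 non-responder.
2. Multiple imputation applies only to data missing for other reasons.
3. Imputation of all missing data is reported as a sensitivity analysis.

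The Withdrawal and Dropout section already has the reason for leaving recorded in the CRF, so the classification can be made blind to group. The Results section reports that no analysis had been done as of May 2025.

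A secondary step, where still feasible and the patient consents, is to collect the scheduled assessments after the lotion is stopped. It comes late: 180 of 200 were enrolled by May 2025 and recruitment was due to end by July 2025. It would also have to go to the ethics committee as an amendment.

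**Cost.** The main change is wording. Reported response rates will look somewhat lower, and power falls modestly: 90.3% with 20% of each arm scored as non-response, but about 82% if the losses are 20% in the treatment arm and 10% in the control arm. The clinical rule on additional treatment is not changed.
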